## Abstract

**Background:** Fragility fractures of the hip are a common injury in England. Meeting post-operative resting energy expenditure (REE) needs are fundamental to recovery from trauma that with greater nutritional intake, post-operative complications and length of stay can be reduced. However, dietary intake can be overlooked when the goal is prompt surgery to reduce pain and lower the risks of mortality at 30 days and 1 year. **Aims:** The primary aim of this study is to observe if post-operative dietary energy intake (kJ/kcal) of older adult hip fracture patients meets their post-operative REE needs to mobilise post-surgery. Secondly, we aim to explore if there is a relationship between length of stay, comorbidity and post-operative complications in relation to dietary intake. **Methods and analysis:** Using a weighed food method, all food and fluid intake from the day of surgery until post-operative day three inclusive will be recorded for a cohort of 30 older adult hip fracture patients. Dietary intake per day will be compared against REE and macronutrient requirements. Baseline sociodemographic and medical history data will be obtained, along with admission data such as malnutrition screening and type of fracture. Regression analysis will be used to explore associations between dietary intake, post-operative complications and length of stay where indicated and to identify if there are areas for further dietary development in this specific patient group. **Ethics and dissemination:** The Health Research Authority approved this study (REC 24/NE/0034). Findings will be published in peer-reviewed, scientific journals and presented at academic conferences.

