### Hypothesis

We hypothesise that older adult hip fracture patients will not be meeting their daily REE needs.We hypothesise that a reduced dietary intake due to participants being unable to meet their daily REE needs because of trauma, anaesthesia and surgery will have a negative impact on LOS and post-operative complications.We hypothesise of an association between reduced dietary intake and a combination of nausea, delirium and pain.To our knowledge, this is the first study to use a weighed food diary for older adult hip fracture patients from the day of surgery (day zero) to post-operative day three inclusive that will not require patient or ward staff recall. With data collection being conducted directly by the researcher, this will increase the accuracy of recording dietary intake.

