### Food diary protocol

The weighed food diary will commence on the participants day of surgery (day zero) and will conclude at post-operative day three inclusive. The weighed food diary will consist of the researcher using an electronic digital kitchen scale with a weight graduation of 1 g (AccuWeight 201, maximum weight 5 kg) to weigh all items served to the participant before and after their mealtime. The researcher will not serve any food directly, with plates or bowls placed directly on the digital scale and recorded by the researcher. Should a food be packaged with a specified weight – for example a yoghurt, said weight on the packaging will be recorded. Fluid intake will be recorded according to each mealtime (e.g. a cup of tea or fruit juice) and the researcher will liaise with the ward staff to log how many jugs of water the participant has consumed daily, and if this has been accompanied with other items such as cordial. A baseline measurement of water jugs, cups and beakers will be taken prior to the study commencing.

The researcher will not be present nor disrupt the participant during their meal, and after their food tray has been retrieved, the researcher will weigh the plate if it is a complete meal (e.g. lasagne), or, if it is a multiple item meal (e.g. meat, potatoes and vegetables), the researcher will weigh the leftover components individually to ensure the validity of the weighed food method and to achieve the highest degree of accuracy possible. After mealtime has concluded, the researcher will briefly ask the participant if they have had any snacks between their meals. Any observed assistance with meals (such as a family member) will be confirmed with ward staff. Additionally, as part of the specific NOF pathway in place, all hip fracture patients regardless of MUST screening assessment are required to consume two oral nutritional supplements (Nutricia™ Fortisip Compact or Fortisip Compact Protein) daily. The researcher will liaise with the ward staff regarding consumption and additionally will record the amount consumed. Data will also be collected regarding the times of meals and the ratio of staff to patients on the ward during each mealtime.

The researcher will liaise daily with the participant's named nurse regarding complications that may develop post-operatively during the study period, such as delirium, pressure ulcers, infection and venous thromboembolism.

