#### Dietary intake

We will analyse if dietary intake is sufficient to meet estimated REE requirements and explore the effect of dietary intake as a predictor of LOS and post-operative complications. Current guidelines will be used to calculate REE, and we will use a factor of 23 kcal/kg actual body weight per day for ‘surgical fixation of a hip fracture’ according to the supporting evidence-based recommendations specified in the guidelines (Todorovic and Mafrici, 2018). Using macronutrient data for hospital meals provided by the trust, consumption and waste per meal will be calculated according to energy (kJ/kcal), protein, carbohydrates, fats and fibre. For any snacks consumed or foods not listed by the hospital, Nutritics v6.00 software will be used for macronutrient data (Nutritics, 2024).

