#### Covariates

LOS data (measured in days) will be obtained from the participants medical records, and the occurrence of post-operative complications will be checked daily with the gatekeeper per participant.

The consent form for participants with capacity and the Consultee Form for participants without capacity were approved by the NHS Ethics Committee. A registered dietitian that is not linked to the study site (CJ) reviewed the study protocol, weighed food diary chart and outcome measures.

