### Data storage and analysis

Participant identifiable data (name, date of birth and hospital number) will be used to create a unique identifier that will ensure the correct food diary data is recorded against the correct patient, when accounting for a participant's potential movement between rooms during their ward stay. Once the participant's LOS and discharge destination data has been obtained, the participant's data will be anonymised and assigned a unique reference number. All participant data will be recorded and held within the trust site to maintain confidentiality and the transfer of patient information once assigned an identifier will be from the research department to the researcher's secure email.

Baseline nutritional requirements for REE, total energy expenditure (TEE), protein, carbohydrates and fat nutritional requirements per day will be calculated according to the specific guideline formula (Todorovic and Mafrici, 2018). In the instance where BMI is outside of the range 18.5 to 30 kg/m^2^, calculation adjustments will be made as per the guideline recommendations (Todorovic and Mafrici, 2018). Regarding physical activity and diet-induced thermogenesis (PAL), a combined factor range of 1.0 to 1.10 will be used, which the guidelines state is a ‘post-surgery factor’ (Todorovic and Mafrici, 2018). In cases where there is a range specified, calculations of nutritional requirements will be made at both the lower and higher scale. Demographic variables will be presented in descriptive summaries such as mean ± SD and median for continuous variables and percentages for categorical variables. For statistical analysis we will present descriptive statistics for REE met per day and to make inferences, we will take an average of the proportion of REE intake of the total food diary.

Multiple regression analysis will be used to explore if REE is a predictor of LOS, with post-operative complications and medical history used as confounders along with those who have capacity or not. Due to a small sample size, we acknowledge that caution should be taken with secondary subgroup analysis. In addition, where REE is met or exceeded, participants food diaries will be scrutinised to explore if this is attributed to a specific category of food (e.g. a high-fat dessert item) and where REE is not met, food diaries will be scrutinised to explore if this is related to complications reported.

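### The length-of-stay regression adjusts for post-operative complications as confounders, although the protocol hypothesises that they result from low intake, so the coefficient may miss part of the association sought

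*Protocol article*

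**What the plan says.** Data storage and analysis sets out the model: "Multiple regression analysis will be used to explore if REE is a predictor of LOS". The same sentence then fixes the adjustment set, so that the model is fitted "with post-operative complications and medical history used as confounders along with those who have capacity or not". For inference, "we will take an average of the proportion of REE intake of the total food diary". I therefore read the predictor as the mean proportion of REE met from day 0 to day 3, although the sentence names REE itself.

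Three other places give complications a different role:
- The Abstract's background states that "with greater nutritional intake, post-operative complications and length of stay can be reduced".
- The second statement under Hypothesis is that reduced intake "will have a negative impact on LOS and post-operative complications".
- The Dietary intake section plans to "explore the effect of dietary intake as a predictor of LOS and post-operative complications".

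Food diary protocol has the researcher ask the named nurse each day about "complications that may develop post-operatively during the study period, such as delirium, pressure ulcers, infection and venous thromboembolism", so complications are not baseline variables. The Covariates subsection opens with "LOS data (measured in days) will be obtained from the participants medical records, and the occurrence of post-operative complications", which puts the dependent variable of the regression and the complications under one label. No LOS model without complications is described.

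**The concern.** A confounder must not be a consequence of the exposure. If low intake leads to complications and complications prolong the stay, complications lie on the path from intake to LOS. Holding them fixed removes that path from the coefficient. What remains is at most a direct association, whereas the second hypothesis concerns the impact of intake on LOS by any route.

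Conditioning on complications can also link intake to anything else that causes complications. Frailty that is not fully captured by the model, and that raises both complication risk and LOS, would then distort the intake coefficient.

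At stake is the reading of the LOS result. A coefficient near zero could mean that intake does not matter, that it matters mainly through complications, or that 30 participants are too few to tell. The planned model cannot separate the first two.

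**Working it through.** The documents give no effect size, SD or complication rate for this model, so there is no stated figure to reproduce. The check has two parts: the roles the text assigns, and an illustration on assumed inputs.

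**Roles assigned to complications**

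| Place | Role |
|---|---|
| Abstract | Reduced by greater intake |
| Hypothesis, second statement | Outcome of reduced intake |
| Dietary intake | Outcome predicted by intake |
| Food diary protocol | Event arising after surgery |
| Data storage and analysis | Confounder of intake and LOS |

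The first four fit together; the fifth does not fit them. The link from complications to LOS is my inference, but entering complications as confounders for LOS already presumes it.

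**What each model estimates**

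Let c be the direct effect of intake on LOS, b the days added by a complication, and δ the change in complication probability per SD of intake. In a linear model, total effect = c + b·δ. Adjusting for complications returns c, so the share removed is b·δ / (c + b·δ).

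**Illustration: intake affects complications**

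All inputs are assumed: complication prevalence about 41%, b = 5 days, log-odds of a complication −0.4 or −0.8 per SD of intake, and c = 0, −1 or −2 days per SD. Each setting used 1,000,000 simulated records.

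| Log-odds per SD | c | Total | Adjusted | Share removed |
|---|---|---|---|---|
| −0.4 | −2 | −2.47 | −2.00 | 19% |
| −0.8 | −2 | −2.85 | −2.00 | 30% |
| −0.4 | −1 | −1.46 | −1.00 | 32% |
| −0.8 | −1 | −1.86 | −1.01 | 46% |
| −0.4 | 0 | −0.47 | −0.01 | about 100% |
| −0.8 | 0 | −0.85 | 0.01 | about 100% |

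For example, 1 − 1.00/1.46 = 0.32.

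**Adding an unmeasured common cause of complications and LOS**

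Assumed strength: 0.7 on the log-odds and 2.1 days of LOS per SD. With c = −1 the adjusted coefficients are −0.88 and −0.80, so even the direct effect is not recovered. With c = 0 the adjusted sign reverses: +0.11 and +0.21, against totals of −0.44 and −0.79.

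**Opposite direction: an early complication lowers intake**

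Assume prevalence p = 0.4, intake lowered by 0.4 or 0.8 (g = −0.4 or −0.8, in units of intake's SD within complication groups), b = 5, and a true effect of −1. The unadjusted coefficient is −1 + 5·g·p(1−p) / (1 + g²·p(1−p)), with p(1−p) = 0.24.
- g = −0.4: −1 − 0.48/1.0384 = −1.46.
- g = −0.8: −1 − 0.96/1.1536 = −1.83.

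Here adjustment recovers −1.0, and the unadjusted model overstates the effect by 46% to 83%.

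**The case against.** The strongest reply is that the protocol does not commit to one direction. Intake is averaged over day 0 to day 3 and complications are logged daily over the same days. The third hypothesis is an undirected association of low intake with nausea, delirium and pain, and the end of Data storage and analysis asks whether unmet REE relates to reported complications. Delirium is one of the named complications; if it suppresses eating and lengthens stay, it is a true confounder. This stands. It rules out treating the unadjusted model as simply correct. It does not justify adjusting for all complications together whatever their onset, because a complication that follows the measured intake cannot confound it.

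Frailty is also not wholly unmeasured. Table 1 collects age, ASA grade, prior mobility, domicile, MUST and medical history. But only medical history and capacity are named for the model, so residual frailty remains a possibility rather than a certainty.

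The analysis is secondary, exploratory and framed largely as correlation, and the authors urge caution because of the sample size. That limits the seriousness of the point, but a small sample does not repair an adjustment set that conflicts with the hypothesis.

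A reader might infer that the planned coefficient must be pulled towards zero, so that a null finding would be an artefact. The documents do not support this. Depending on the true structure, adjustment can attenuate, reverse the sign or give the right answer, and with 30 participants a null may simply be imprecise. Nor are complications neglected as an outcome: the Abstract, Research aims and Dietary intake sections all plan to relate them to intake.

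**Conclusion.** The inconsistency is in the text. The protocol treats complications as a result of low intake in three places, then adjusts for them as confounders in its only specified regression, with no alternative model. Under its own second hypothesis the LOS coefficient could omit the route through complications, and a null could not count against that hypothesis.

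The size is unknown. The range of 19% to 100% of the total effect rests wholly on assumed prevalence, days per complication and effect strengths, on intake preceding complications, and on no unmeasured common cause. If complications precede low intake, the bias lies with the unadjusted model instead. The point should be fixed before the LOS model is run, but it does not affect recruitment, data collection or the primary question of whether intake meets REE.

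**What to change.** In Data storage and analysis:
1. Make the main LOS model adjust for pre-operative variables only: medical history, capacity and, for example, age or ASA grade from Table 1. With 30 participants the list should stay short. Name the predictor as the proportion of REE met.
2. Analyse complications as a separate outcome of intake, in line with the hypothesis.
3. Report the complication-adjusted LOS model beside the main one, labelled as a direct association.
4. Use the existing daily checks to record the onset day of each complication. Add a sensitivity analysis that separates complications preceding the measured intake from those following it.

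List LOS and complications as outcomes rather than under Covariates, so that the labels agree.

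The cost is one extra model, the sensitivity analysis, an onset-day field and some wording. The downside is that early complications which reduce intake stay unadjusted in the main model. That model may then overstate the effect, which is why the two models should be read together with the onset-day analysis.

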Research exploring the specific dietary intake of older adult hip fracture patients is also limited. Most recently, a short report of weighed lunch and dinner intake (excluding fluids), found dietary intake was poor (‘nutritionally vulnerable patients’ (*n* = 15) mean (SD): 643 (354) kcal/day), regardless of ‘good nutrition practice’ according to NHS England issued guidance (Sahota et al., 2023). However, methodological quality was poor owing to the type of study, with a lack of clarity regarding how intake was assessed, and the weighed element suggested to be only ‘total plate waste’ for the ward inclusive. Additionally, whilst the study claimed to focus on nutrition practice, there was no breakdown of macronutrients other than protein and no analysis of food diary data, but rather an exploration of food waste. In an earlier study that explored the dietary intake of hip fracture patients, only 59% of energy needs were met (week 2, 3-day intake; 4219 ± 319 kJ/day, kcal not stated), however, the authors stressed the importance of ‘early nutritional assessment’ but did not commence the food diary until post-operative week 2, and excluded those with cognitive impairment, which limits its generalisability (Nematy et al., 2006). Additionally, whilst the study analysed energy requirements according to basal metabolic rate (BMR), newer guidelines developed by the British Dietetic Association (BDA) and the Parenteral and Enteral Nutrition Specialist Group (PENG) state that resting energy expenditure (REE) is a more appropriate measure in estimating the nutritional requirements of adults when acutely unwell (Todorovic and Mafrici, 2018).

The standard approach in hospital for monitoring in-patient dietary intake is a visual estimation method (VEM), such as a ‘quarter’ or ‘half’ of a meal or expressed as a percentage (Heighington-Wansbrough and Gemming, 2022). However, the validity of this method is questionable on account of the potential for inaccuracy and variability between staff. In a systematic review of 14 studies using varying VEM methods, underestimation ranged from <2% to 53% in 5 studies, and overall, training was identified as a crucial factor in relation to compliance and accuracy (Hirsch et al., 2021). Although a weighed food diary was cited as the ‘gold standard’ for measuring dietary intake, in a ward context, this can be an arduous task.

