### Research aims

The primary aim is to observe if the post-operative dietary energy intake (kJ/kcal) of older adult hip fracture patients meets their REE needs that would allow for basic movements, such as from bed to chair and initial mobilisation with a physiotherapist post-surgery.

Secondly, the aims of the study are to explore if there is a correlation between post-operative dietary intake and LOS; to explore the relationship between comorbidity (where reported) and post-operative dietary intake, according to dietary intake; and to explore (if) in the development of post-operative complications (including, delirium, infection, pressure ulcers and venous thromboembolism), there is a correlation with post-operative dietary intake.

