### Study sample

The study aims to recruit 30 older adult hip fracture patients admitted to an orthopaedic trauma ward for surgical repair of a hip fracture. A district general sized hospital was chosen as opposed to the scale of a trauma/transplant centre hospital to confer greater generalisability to the population in England with the findings from this study. A sample size of 30 was agreed by the research team based on the admissions data published by the NHFD for the specific study site and is reflective of a ‘typical’ average month of admissions to the hospital, according to 2021 and 2022 data. The decision to enrol 30 patients was primarily based on funding constraints, as there are currently no available funds to support a larger sample. This number was chosen to ensure we can gather detailed and meaningful data while adhering to our timeline and resources. The recruitment period will last for a continuous period of 4 weeks, and all eligible patients according to the inclusion and exclusion criteria will be invited into the study via the gatekeeper as they are admitted to the hospital ward. The standard diagnosis for a hip fracture is an x-ray on admission to the accident and emergency department, following which, the participant's care adheres to a specific ‘neck of femur (NOF) fracture pathway’ which is already in place at the study site.

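### The exploratory diary review looks for a food category only where REE is met and for complications only where it is not, so taken alone it cannot separate association from coincidence

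*Protocol article*

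**What the plan says.** The last sentence of the analysis text in Data storage and analysis sets up two searches. On one side, "where REE is met or exceeded, participants food diaries will be scrutinised to explore if this is attributed to a specific category of food". On the other, "where REE is not met, food diaries will be scrutinised to explore if this is related to complications reported". The sentence is framed as an addition to the main analysis and as exploration. It follows a caution about subgroup work in a small sample.

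Elsewhere the article states wider intentions for complications:

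- Research aims asks whether, when complications develop, "there is a correlation with post-operative dietary intake".
- The Abstract says "Regression analysis will be used to explore associations between dietary intake, post-operative complications and length of stay where indicated".
- The Dietary intake section says the study will "explore the effect of dietary intake as a predictor of LOS and post-operative complications".
- The Discussion repeats the correlation aim.

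The one regression that Data storage and analysis spells out takes length of stay (LOS) as the outcome and REE as the predictor. Complications, medical history and capacity enter it as confounders.

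The cohort is single and small: "The study aims to recruit 30 older adult hip fracture patients". On the reason for that number, "The decision to enrol 30 patients was primarily based on funding constraints".

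**The concern.** The review sorts diaries by the outcome and then offers each side its own explanation. To say that a shortfall goes with complications, one needs the frequency of complications where there was no shortfall. To say that success is due to a type of food, one needs to know how often that food was eaten by those who fell short. The planned wording is explanatory, but neither piece of information is part of the review.

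The food question is the more exposed. Patients eat from one hospital menu, and the Food diary protocol section says that every hip fracture patient on the pathway is required to take two oral supplements a day. An item that supplies much of the energy in diaries meeting REE may be just as common in the others, and the review as written would not show it.

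What is at stake is how the secondary explanations are drawn. The Introduction and Discussion hope that the study as a whole will inform practice recommendations and staff training, so a one-sided observation could be read as more than it is.

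**Working it through.** **1. What is asked of whom.** The article gives no figure to reproduce here, so the first check sets the texts side by side.

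| Question | Diaries meeting REE | Diaries not meeting REE | Comparison described elsewhere in the article |
|---|---|---|---|
| Food category | Yes | Not stated | None |
| Complications | Not stated | Yes | Intended for the whole cohort (Abstract, Research aims, Dietary intake, Discussion), but not the outcome of the regression detailed in Data storage and analysis |

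The data would support both comparisons. The Covariates section has complications checked daily for each participant, and the Dietary intake section has energy and macronutrients calculated per meal without restriction by REE status.

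**2. What the one-sided complications review shows if there is no association.** Let n be the number of patients not meeting REE and c a complication rate that is the same on both sides. Both are assumptions, as the article gives neither.

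P(at least one) = 1 − (1 − c)^n. For n = 27 and c = 0.10 this is 1 − 0.9^27 = 1 − 0.058 = 0.94.

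P(at least three) = 1 − Σ C(n,k) c^k (1 − c)^(n−k) for k = 0, 1, 2. For n = 27 and c = 0.10 this is 1 − (0.058 + 0.174 + 0.252) = 0.52.

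| n not meeting REE | c | Expected cases n × c | P(≥1) | P(≥3) |
|---|---|---|---|---|
| 15 | 10% | 1.5 | 0.79 | 0.18 |
| 15 | 30% | 4.5 | 0.995 | 0.87 |
| 24 | 10% | 2.4 | 0.92 | 0.44 |
| 24 | 30% | 7.2 | 0.9998 | 0.99 |
| 27 | 10% | 2.7 | 0.94 | 0.52 |
| 27 | 20% | 5.4 | 0.998 | 0.93 |
| 27 | 30% | 8.1 | 0.9999 | 0.995 |

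Some co-occurrence is likely in most of these cases. It is not certain when the rate is low or the group small.

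**3. How many patients might meet REE (illustration only).** The Introduction cites an earlier study in which "only 59% of energy needs were met". With a normal distribution, mean 59% and an assumed SD of 20, 25 or 30 points, P(≥100%) = 1 − Φ(41/SD) = 0.020, 0.051 or 0.086. Multiplied by 30, that is 0.6, 1.5 or 2.6 patients.

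The input does not transfer well: that study's diary began in post-operative week 2, and its requirement was based on basal metabolic rate. Its intake of 4219 kJ/day is 4219/4.184 ≈ 1008 kcal/day. Set against this protocol's 23 kcal/kg at assumed weights of 70, 60 and 50 kg (1610, 1380 and 1150 kcal), it is 63%, 73% and 88% of REE. With SDs of 20 to 30 points, about 0.9 to 3.2, 2.7 to 5.5, or 8 to 10 of 30 patients would then meet REE. The plausible range is therefore wide, from almost none to about a third.

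**4. What a met/not-met comparison could deliver.** Fisher's exact test, nominal two-sided 5%, by exact enumeration; the rates are assumed, with the higher one in the not-met group.

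| Split (not met/met) | Power, 40% v 10% | Power, 60% v 10% |
|---|---|---|
| 15/15 | 0.33 | 0.74 |
| 20/10 | 0.30 | 0.74 |
| 24/6 | 0.06 | 0.49 |
| 27/3 | 0.001 | 0.13 |

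At a common 30% rate the type I error is 0.017 to 0.031 over these splits. The comparison removes the one-sidedness, but with few patients meeting REE it can only describe. Using the continuous proportion of REE met keeps all 30 patients and avoids the split.

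**The case against.** The strongest reply is that the article does plan to relate complications to intake in everyone, and says so in four sections. A reader of the quoted sentence alone might infer that neither explanation has any comparison group. For complications the documents do not support that, and this part of the reply stands. Its weight is limited, because the only regression detailed in Data storage and analysis does not have complications as its outcome. Within that section, the one-sided review is the only analysis that relates them to intake. For food category the reply has nothing to point to.

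A second reply is that the review is an exploratory extra with no test or decision rule, and that a review asking whether something is related may answer no. This also stands. A reader might infer that an explanation is bound to be found by construction; the documents do not show that, and step 2 gives likely co-occurrence, not certainty. But the article's caution is about small numbers, and a larger sample would not supply the missing comparison.

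Third, the sentence does not say whether REE is met by a patient or on a day, and the same section reports REE met per day as well as the diary average. If days are meant, the patient-level counts above do not apply directly. The asymmetry remains.

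Finally, a review form is the kind of detail an article leaves to the full protocol. That is fair as to the form. The point here rests on the rule that the article does state.

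**Conclusion.** The point holds as a minor to moderate one about interpretation. The stated review asks each question on one side of the outcome only. By itself it cannot support attributing met REE to a food category, or relating unmet REE to complications. The gap is complete for food category and partial for complications, where a cohort-wide aim exists without a matching analysis in Data storage and analysis.

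On size, chance co-occurrence of shortfall and complications is probable under most assumed rates and group sizes, with P(≥3) from 0.18 to 0.995 in the cases shown. These figures rest on assumed complication rates and splits. The number of patients expected to meet REE is illustrative only, since it depends on an assumed SD and a 59% figure from a different setting; no conclusion should hang on it. The primary aim, whether intake meets REE, is unaffected.

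**What to change.** - Put both questions to all diaries, using the same form whether or not REE is met: energy share by food category, and complications with day of onset.
- Relate both items to the continuous proportion of REE met in all participants. The section already averages this proportion over the diary.
- Show the met/not-met breakdown side by side only as description, and state whether the unit is the patient or the day.
- Label the review descriptive, and link its complications part to the cohort-wide aim in Research aims.

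Onset day is worth recording because the Hypothesis section places delirium among the factors associated with reduced intake, while Research aims lists it as a complication; the order of events bears on which reading is open.

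The cost is a little extra review of up to 30 diaries. Food is weighed and complications are checked daily for every participant, so no new data are needed.
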